#### Random Assignment

After completing the baseline assessment, participants were assigned to a condition through an urn randomization procedure. The urn randomization procedure provided balance across age (18-24 and 25-34 years), race/ethnicity (Latino/Hispanic and all other race/ethnicities), and HIV care continuum status (linked, nonlinked to HIV care). Participants were randomized into 1 of the 2 conditions: Group A—immediate text message intervention delivery (n=61) or Group B—delayed text message intervention delivery (n=69) whereby participants were delivered the text-messaging intervention after a 90-day delay period. Both groups received the same 90-day text-messaging intervention. The randomized 2-group repeated measures design assessed participants at 3, 6, 12, and 18 months post randomization.

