Outcome data were generated through 2 mechanisms: (1) assessments performed onsite at baseline and at 3, 6, 12, and 18 months post baseline and (2) electronic medical record (EMR)/electronic health record (EHR) data abstraction. In each case, data were imported from delimited text format (ie, .csv, the native format for the cloud-based data storage, scanned paper assessments, and extracted EMR/EHR data) into Stata v13SE (StataCorp).

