##### HIV Health Assessment

Originally developed by the principal investigator (PI) [name], for an intensive prevention case management intervention, this instrument records demographics (eg, sexual identity, age, and racial/ethnic identities), educational attainment, housing status, access to insurance, HIV treatment status (including position in the HIV care continuum), HIV medication status (including medication type and dose) and self-reported ART adherence, and barriers to receiving HIV care [49]. Only the domains specific to the outcome measurements of this study that did not duplicate the ETAC cross-site evaluation were used.

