### Statistical Analyses

Table 2 provides all evaluation outcomes and their chosen measurement models. Power calculations are based on assumptions of alpha=.05 (2-tailed tests), a sample size of 130 HIV-positive young transgender women, and a power standard of 0.80. It was calculated that logistic regression analyses of primary outcomes would be able to find a minimum detectable odds ratio of 2.98 for linkage/uptake of ART and achievement of an undetectable viral load (the primary outcomes of interest).

**Table 2 table2:** Study outcomes and measurement models.

Primary outcome	Measurement model
Linkage to HIV primary care (self-report and EMR^a^/EHR^b^ abstraction)	0= Participant did not attend HIV medical visit within 3 months of enrollment; 1= Participant attended within the first 3 months
Prescribed ART^c^ medication (self-report and EMR/EHR abstraction)	0=Participant is not prescribed HIV medication; 1=Participant is prescribed HIV medication
Retention in HIV primary care (self-report and EMR/EHR abstraction)	0=Participant did not attend a second HIV care appointment after the initial 3 months; 1=Participant attended an additional HIV primary care visit after the initial 3 months
ART adherence (self-report)	Ordinal scale (Likert)
Viral load monitoring (self-report and EMR/EHR abstraction)	Binary (0=>200 copies/mL, 1=<200 copies/mL)

^a^EMR: electronic medical report.

^b^EHR: electronic health report.

^c^ART: antiretroviral therapy.

All regression analyses assess assumptions of normality and model fit. In addition to the primary outcomes listed in Table 2, participants were assessed for changes in their HIV-related self-efficacy from baseline to follow-up evaluations. The HIV-ASES scale was used to assess HIV self-efficacy, producing continuous values suitable for ordinary least squares (OLS) regression. In addition, if during implementation, a sufficient number of participants opted in to receive one or more of the postintervention retention/engagement text messages available through final distal follow-up evaluation, additional analyses were carried out to estimate the observed effect(s) of receiving these postintervention text messages.

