All calculations of detectable effects for primary outcomes were based on expected cultural/demographic subgroup analyses premised on known social determinants of risk (eg, racial/ethnic identity, language and health insurance) and are displayed in Table 2. Secondary analyses related to HIV self-efficacy were analyzed using OLS regression and should produce detectable effects at *f*^2^=0.067. Given these values, detectable effects of all analyses should, if benchmarked, fall in the *small to moderate* to *moderate* ranges. Given an expected follow-up rate of at least 85% (111/130) at each time point, associations between primary outcomes and optional postintervention retention/engagement messages should produce minimum detectable effects exhibiting a 3% (repeated measures survival analysis testing time-based dichotomous outcomes, eg, linkage) to 18% (OLS regression for secondary analyses, eg, HIV-related self-efficacy scores) increase in detectable effect size (ie, outcomes will be more difficult to detect), resultant from participant attrition.

Primary outcome analyses comprised bivariate contrasts of outcomes over time (ie, HIV care continuum outcomes at baseline and each follow-up, with differences tested via *t* test and chi-square analyses) and multivariate analyses of these same outcomes regressed on random study arm assignment, self-reported exposure to theory-based text messages, and time. Observations were nested within participants, and sociodemographic controls were tested for inclusion during sensitivity testing of the models. Secondary outcomes included sexual risk behaviors, substance use, self-efficacy, and changes in gender identity over time.

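### Linkage and retention are defined by visits after enrollment, so the planned baseline-to-follow-up contrasts and time term do not fit these two of the five primary outcomes

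*Protocol article*

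**What the plan says.** Two parts of the Statistical Analyses section of the protocol article bear on this.

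- **Outcome definitions (Table 2).** Linkage to HIV primary care is coded "0= Participant did not attend HIV medical visit within 3 months of enrollment; 1= Participant attended within the first 3 months". Retention takes the value 1 as follows: "1=Participant attended an additional HIV primary care visit after the initial 3 months". Both appear in the list of five primary outcomes.
- **Primary analysis.** The bivariate part contrasts "HIV care continuum outcomes at baseline and each follow-up, with differences tested via" t test and chi-square. The multivariable part is described as "multivariate analyses of these same outcomes regressed on random study arm assignment, self-reported exposure to theory-based text messages, and time". The text adds: "Observations were nested within participants". No outcome is exempted from either part.

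Under Evaluation Procedures, the measurement schedule is "assessments performed onsite at baseline and at 3, 6, 12, and 18 months post baseline", together with abstraction from electronic medical records.

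Two other places mention care status at entry. Random Assignment balances the urn on "HIV care continuum status (linked, nonlinked to HIV care"), and the HIV Health Assessment records "HIV treatment status (including position in the HIV care continuum"). Neither is said to be the Table 2 outcome or to supply its baseline value.

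**The concern.** A before-after contrast needs the same quantity measured on both occasions. Linkage and retention, as coded in Table 2, count only visits made after enrollment, so no woman can have met either definition on the day she enrolls. A difference between baseline and follow-up then says little about care: a woman already in care who keeps one routine appointment would appear to have changed.

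At stake is how any reported improvement over time in linkage or retention would be read. Such a result could be highly significant in both arms and still not distinguish useful text messages from inert ones. The same holds for the time coefficient in the repeated-measures model. Linkage is also one of the outcomes named in the article's power statement, so this is not a minor endpoint.

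**Working it through.** **1. The plan's own figure.** The one number given for linkage is a minimum detectable odds ratio of 2.98 (N=130, two-sided alpha .05, power 0.80). No reference rate is stated, so it can be neither confirmed nor refuted. With 65 women per arm it is reached at a reference rate of about 0.20 or about 0.58, and over reference rates of 0.10 to 0.70 the minimum detectable odds ratio runs from 2.70 to 3.74. The point here does not depend on it.

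**2. Definitions against the visit schedule.**

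| Outcome (Table 2) | Baseline | 3 mo | 6 mo | 12 mo | 18 mo |
|---|---|---|---|---|---|
| Linkage | none | determined | fixed | fixed | fixed |
| Retention | none | none | can be scored | can be scored, cannot fall | can be scored, cannot fall |
| ART prescription, adherence, viral load | status | status | status | status | status |

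The retention row assumes cumulative scoring (ever attended since month 3). The last row holds measures of current status, which can be taken in the same way at every visit.

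**3. The possible readings of baseline.** The article does not say how linkage or retention is coded at baseline. There are three options:

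- *Missing.* The stated contrast cannot be run.
- *Taken from another variable*, such as the urn factor. The contrast then compares care status before enrollment with attendance after it, which are different quantities.
- *Coded 0 for every woman.* The rise is built in.

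**4. Size under the third reading (an assumption).** Each woman is her own control and nobody can move from 1 to 0, so all k attenders are discordant in the same direction. The two-sided exact McNemar P value is 2 × 0.5^k:

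- k = 4: 2 × 0.0625 = .125
- k = 5: 2 × 0.03125 = .0625
- k = 6: 2 × 0.015625 = .031

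Six attenders of 130 (6/130 = 4.6%) are therefore enough. The chance of at least 6 attenders when the intervention does nothing is the binomial tail P(X ≥ 6). The attendance rates below are assumed.

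| Assumed 3-month attendance | n = 130 | n = 111 (85% follow-up) |
|---|---|---|
| 5% | 0.64 | 0.48 |
| 10% | 0.99 | 0.97 |
| 20% | >0.999 | >0.999 |

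**5. Retention scored cumulatively.** Suppose a constant 20% of women who have not yet attended do so in each 3-month interval, with no intervention effect (again assumed). After m intervals beyond month 3 the proportion is 1 − 0.8^m. With m = 1, 3 and 5 at months 6, 12 and 18:

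- month 6: 1 − 0.8 = 0.20
- month 12: 1 − 0.512 = 0.49
- month 18: 1 − 0.328 = 0.67

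The time trend is steep although behavior is constant.

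**The case against.** The strongest reply is that the article is a condensed account and that baseline care status is in fact collected, both as an urn factor and in the HIV Health Assessment. The phrase about continuum outcomes at baseline could refer to that status, with the coding left to an analysis plan not shown. This stands in part: a reader should not infer that no baseline continuum data exist. But the article offers Table 2 as the measurement models for all evaluation outcomes and then applies the primary analysis to those same outcomes. Using a different baseline variable would still compare unlike quantities. The conflict lies between two stated rules and is more than an omitted detail.

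A second reply is that the article mentions repeated-measures survival analysis for time-based outcomes such as linkage. That remark concerns detectable effects for the optional post-intervention messages and does not replace the stated primary analysis.

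Several stronger readings are tempting but unsupported:

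- *Every woman is scored 0 at baseline and her linkage result is copied to later visits, so that the nested model is degenerate.* The article states neither step.
- *Four attenders already give P=.04.* That is an uncorrected chi-square treating the same women as two independent samples. The exact paired test gives P=.125, and six are needed.
- *Retention has no value at any visit.* It can be scored at 6, 12 and 18 months.
- *The trial's randomized evidence is compromised.* A rise common to both arms does not by itself create a difference between them.

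**Conclusion.** The point holds for two of the five primary outcomes and is confined to the before-after contrasts and the time term. As Table 2 defines them, linkage and retention do not support these analyses under any of the three readings of baseline. The logical conflict needs no assumption. The numerical illustration does: it rests on a baseline coded 0 and on assumed attendance rates.

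The comparison of linkage between arms at month 3 remains valid, and it falls before Group B starts its messages. ART prescription, adherence and viral load can be analysed repeatedly as planned. This should be corrected, but it does not threaten the main randomized comparison of linkage.

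**What to change.** Reword the analysis plan as follows.

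1. Take linkage and retention, as now defined, out of the baseline-to-follow-up contrasts and the repeated-measures model.
2. Analyse linkage once per woman, as a binary outcome at month 3 compared between arms.
3. Analyse retention once per woman over one stated window, compared between arms. State that Group B has begun the intervention by then, so this is a contrast of immediate with delayed delivery and not of messages with no messages.
4. If change over time is wanted, define one indicator identically at every time point including baseline, for example any HIV care visit in a fixed look-back period, from dated EMR/EHR records.
5. Keep the repeated-measures model for ART prescription, adherence and viral load.

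The cost is a small amount of rewording and the loss of a nominal longitudinal analysis for two outcomes. Record abstraction is already part of the study, so steps 1 to 3 and 5 need no new data collection. Step 4 needs the abstracted visits to be dated and to reach back before enrollment. The article says the primary analyses start only after follow-up ends, so the change can be made before they are run.

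### The primary model as listed does not isolate month 3, the only visit that compares treated with untreated women as randomised; a common arm effect over months 3 to 18 would be heavily attenuated

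*Protocol article*

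**What the plan says.** Under Random Assignment, Group A (n=61) starts the messages at once. Group B is described as "delayed text message intervention delivery (n=69) whereby participants were delivered the text-messaging intervention after a 90-day delay period", and the article adds: "Both groups received the same 90-day text-messaging intervention". Assessments are at 3, 6, 12 and 18 months after randomisation.

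Under Statistical Analyses, the primary outcome analyses have two parts. The first is a set of bivariate contrasts over time, covering baseline and each follow-up, by t test and chi-square. The second is "multivariate analyses of these same outcomes regressed on random study arm assignment, self-reported exposure to theory-based text messages, and time", with observations nested within participants. No interaction between arm and time, no time-varying treatment indicator and no primary visit is named.

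Table 2 scores linkage by attendance within 3 months of enrolment. Retention is scored as "1=Participant attended an additional HIV primary care visit after the initial 3 months". ART prescription, adherence and viral load have no time window in the table.

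The power statement reads "Power calculations are based on assumptions of alpha=.05 (2-tailed tests), a sample size of 130 HIV-positive young transgender women, and a power standard of 0.80". From these inputs the article arrives at a "minimum detectable odds ratio of 2.98 for linkage/uptake of ART and achievement of an undetectable viral load".

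**The concern.** A delayed-start design carries a randomised comparison of messages with no messages only while the delayed arm is waiting. Here that is the first 90 days, and one visit falls at the end of it. From month 6 on, both arms have had the full course, and an arm difference then describes the timing of delivery.

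A model with arm and time as separate terms gives arm one coefficient, an average over one informative visit and three visits where both arms are treated. That average does not estimate the effect of the messages. The detectable effect in the power statement is plausible for a single two-arm contrast and does not carry over to such an average.

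Self-reported exposure adds a second difficulty. It is measured after randomisation, and at month 3 Group B has not yet been sent any intervention messages, so exposure is closely tied to arm at the one visit that matters. Adjusting for it removes part of the randomised contrast.

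At stake is the main conclusion on viral suppression, which the abstract calls the desired outcome. An effective intervention could end with a weak and non-significant arm coefficient.

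**Working it through.** **Inputs from the article.** Two-sided alpha 0.05, power 0.80, N=130, arms of 61 and 69, detectable odds ratio 2.98, visits at months 3, 6, 12 and 18, Group B's course from day 90 to day 90 + 90 = 180, expected follow-up 85% (111/130).

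**Inputs assumed.** Control-arm event rate, within-person correlation and persistence of the effect. The article gives none of them, so ranges are shown.

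**1. The plan's own figure.** Without a control rate, 2.98 cannot be strictly reproduced. A two-proportion calculation with 69 against 61 returns 2.98 at a control rate of about 0.20 or 0.57. For control rates from 0.20 to 0.55 the detectable odds ratio is 2.71 to 2.96. With 111 completers, 2.98 corresponds to a rate of about 0.30 or 0.43. The figure is plausible for one two-arm contrast.

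**2. Averaging by hand.** Give the four visits equal weight and write each arm difference as a fraction of ln 2.98 = 1.092.

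- Effect persists and Group B catches up by month 6: differences 1, 0, 0, 0. Mean 1.092/4 = 0.273, odds ratio exp(0.273) = 1.31. With baseline as a fifth visit: 1.092/5 = 0.218, odds ratio 1.24.
- Effect fades (Group A at 1, 0.5, 0, 0; Group B at 0, 1, 0.25, 0): differences 1, -0.5, -0.25, 0. Mean 0.25/4 x 1.092 = 0.068, odds ratio 1.07.

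**3. Simulation.** Repeated binary outcome, 61 against 69, 15% missing at each visit, true odds ratio 2.98 for treated against untreated, 300 to 500 runs per setting, logistic GEE. Power counts results significant at two-sided 0.05 in favour of Group A, so with no effect it would be about 2.5%.

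| Control rate, latent correlation | Arm + time, persists | Arm + time, fades | Month-3 contrast |
|---|---|---|---|
| 0.20, 0.4 | OR 1.30, 13% | OR 1.05, 5% | OR 3.0, 73-75% |
| 0.45, 0.4 | OR 1.42, 23% | OR 1.09, 5% | OR 3.1-3.2, 81-82% |
| 0.45, 0.3 | OR 1.35, 22% | OR 1.06, 3% | OR 3.0, 77% |
| 0.45, 0.6 | OR 1.45, 25% | OR 1.07, 5% | OR 3.0, 83% |

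If Group B has reached only 75% of the effect at month 6, the pooled odds ratio is about 1.5 with 27-38% power. With no crossover at all, the same pooled model returns 2.95 to 3.00 with 97-100% power, so the loss comes from the crossover and not from the model class.

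A separate simulation with untreated suppression 30%, treated 56%, correlation 0.5 and no stated attrition gave pooled odds ratios of 1.30 (power 18%) for a persisting effect and 1.19 (power 12%) for a fading one. Its month-3 power of 87-89% is higher than the table shows, and the table's 73-83% is the better guide because the plan expects about 15% loss.

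**4. Adding exposure.** Exposure was set to a reading level unrelated to outcome, and to zero before a woman's messages start. With correlation 0.4, the arm odds ratio at control rates 0.20 and 0.45 falls to 1.23 and 1.30 (power 10% and 17%) if effects persist, and to 0.98 and 1.01 (power 3%) if they fade.

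**5. Outcome by outcome.** Linkage closes at month 3, before Group B starts, so it is a clean randomised comparison. Retention opens at month 3, just as Group B's messages start. ART prescription, adherence and viral suppression are open to the averaging above. The figures are for a binary outcome; for adherence, which is ordinal, the direction carries over but the size was not computed.

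**The case against.** The strongest reply is that the article lists predictors and does not write out a model. An arm-by-time term is neither stated nor excluded, and such detail often sits in the full plan. A reader might infer that the trial definitely fits one constant arm effect; the text does not establish that. What stands is that the article does name the terms of its primary model, and those terms, taken as given, do not isolate the randomised comparison.

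Second, bivariate contrasts at each follow-up are also primary and would include month 3. They are described as contrasts over time, not as contrasts between arms, and month 3 has no priority among them. They soften the point without settling it.

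Third, the exposure term could carry part of a treatment effect in both arms, so the arm coefficient is not the only place an effect could appear. That is true, but exposure is not randomised and cannot stand in for the randomised contrast.

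Fourth, a reader might conclude that every primary outcome is diluted. Linkage is not.

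Fifth, a reader might say that retention never has an untreated comparator and would be null however well the messages work. That goes too far. A second visit may depend on linkage during months 0 to 3, when the arms do differ, and Group B is only beginning its course when the window opens.

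**Conclusion.** The point holds in this form: month 3 is the only randomised comparison of treated with untreated women, the article gives it no special standing, and the model as listed would average it with three visits at which both arms have been treated. For the binary repeated outcomes, a true odds ratio of 2.98 would appear as about 1.3 to 1.45 (power about 13-25%) if effects persist, and about 1.05 to 1.2 (power about 3-12%) if they fade, against about 3 (power about 73-83%) at month 3. Adjustment for exposure worsens this.

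The sizes rest on assumed control rates, correlation and persistence, and on reading the listed terms as main effects. It would be too strong to say that the effect shrinks to almost nothing or that a true effect would be reported as null. About a quarter of the log odds ratio survives if effects last, and near-null values need a fading effect, on which the article gives no figure.

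**What to change.** State that the between-arm difference at month 3 is the primary efficacy contrast for ART prescription, adherence and viral suppression. Estimate it from an arm-by-visit model or from a model of month 3 alone, in either case without adjustment for self-reported exposure. Any exposure analysis should be separate and labelled as non-randomised.

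Keep linkage as defined. Report arm differences at months 6, 12 and 18, and retention, as immediate versus delayed delivery and not as messages versus no messages. Retention may stay a listed outcome if it is interpreted in that way.

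The cost is a change of analysis wording, to be made before the primary analyses begin, which the article places after follow-up ends. No new data are needed. The downside is that months 6 to 18 no longer carry the efficacy claim.

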### Evaluation Procedures

The evaluation plan for *Text Me, Girl!* was 2-fold, with both a cross-site and a local evaluation. Under the sponsorship of the HRSA Special Projects of National Significance (SPNS) Social Media Initiative**,** the Evaluation and Technical Assistance Center (ETAC) at University of California, Los Angeles, was responsible for providing technical assistance and capacity building to the local demonstration sites on clinical and program activities and leading the cross-site evaluation. The cross-site evaluation included both a behavioral and clinical assessment. The clinical assessments were carried out by a medical care provider at one of the collaborating HIV medical care clinics. Once data were collected and abstracted by the HIV medical care provider, FRI submitted the data to ETAC via a Web-based system called the ETAC Social Media Project Portal.

For the local evaluation component, the outcomes were selected based on HRSA priorities and the Los Angeles Enhanced Comprehensive HIV Prevention Plan [17]. *Text Me, Girl!* collected and reported on the required performance measures, including program-specific and required ETAC data at baseline and at follow-up data visits administered at 3 months post enrollment, and approximately 6, 12, and 18 months post enrollment. The project director, research coordinator/evaluator, and RAs were trained in administration of the assessments and on the procedures to be used for data submission to HRSA.

In addition to the local and cross-site assessments, process evaluation and study monitoring were also carried out as part of the overall evaluation of *Text Me, Girl!*. Process evaluation procedures included the following: (1) formative evaluation of the study to update and refine study components that were responsive to the needs of young HIV-positive transgender women, (2) process monitoring of the delivery of the study, and, (3) process evaluation of successful linkage, engagement, and retention among participants. An intervention exposure (IE) question was administered as part of the reporting protocol. Using the study mobile phone, an RA sent a monthly IE text message to each participant on a Wednesday afternoon between 3:00 pm and 7:00 pm. The IE text message was as follows: “In the past month, how many of the text messages did you read? Please text back one of the following: 1) none, 2) some but less than half, 3) about half, 4) a lot but not all, or 5) all.”

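### The primary model sets self-reported message reading beside randomised arm, so its arm coefficient is not the randomised effect in the first 90 days, the only controlled period

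*Protocol article*

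**What the plan says.** Statistical Analyses describes two kinds of primary analysis. One is a set of bivariate contrasts of care-continuum outcomes over time, from baseline to each follow-up; it is not described as a comparison between arms. The other is multivariate: the same outcomes "regressed on random study arm assignment, self-reported exposure to theory-based text messages, and time", with observations nested within participants. Sociodemographic controls are left to sensitivity testing; exposure is not.

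Evaluation Procedures defines the exposure item as a monthly text asking "In the past month, how many of the text messages did you read", answered on five levels from none to all.

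Under Random Assignment, 61 women were allocated to immediate delivery and 69 to delayed delivery. For the delayed group, "participants were delivered the text-messaging intervention after a 90-day delay period". The section adds: "Both groups received the same 90-day text-messaging intervention". Assessments are at 3, 6, 12 and 18 months. Table 2 defines the linkage outcome by attendance within 3 months of enrolment.

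The power statement assumes "alpha=.05 (2-tailed tests), a sample size of 130 HIV-positive young transgender women, and a power standard of 0.80" and gives a "minimum detectable odds ratio of 2.98 for linkage/uptake of ART and achievement of an undetectable viral load".

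**The concern.** Randomisation protects the comparison of arms as allocated. It does not protect a comparison conditional on something that happens afterwards. How much a woman reads is decided after allocation and by her, and reading is how a text-message programme would be expected to work.

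With arm and reading in one model, the arm coefficient compares the groups at equal reading. At month 3 the only level the groups share is no reading (if Group B is coded that way), so the coefficient is an extrapolation to Group A women who read nothing. Three things can follow: the part of the effect carried by reading is taken out of the arm term; any tendency of engaged women to do better anyway is subtracted from the arm term; and the standard error rises because arm and exposure are strongly correlated. Month 3 is the only assessment before Group B's delivery and the window that defines linkage. The article states no primary comparison of arms without exposure.

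**Working it through.** **The plan's own figure.** The detectable odds ratio of 2.98 is stated without a control rate, so it can be neither confirmed nor refuted. It is attainable: at 61 vs 69, two-sided alpha 0.05 and power 0.80, a two-proportion calculation gives 2.96 at a control rate of 0.20, 2.71 at 0.40 and 3.07 at 0.60. It is used below as the assumed true effect.

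**Inputs.** From the article: 61 vs 69; OR 2.98; five reading levels; no messages to Group B before day 90. Assumed: control rate 0.40; Group A reading distribution 5/15/20/30/30% over levels 1 to 5; Group B all at level 1.

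**Step 1, reading in Group A.**
- Mean = 0.05×1 + 0.15×2 + 0.20×3 + 0.30×4 + 0.30×5 = 3.65, which is 2.65 levels above none.
- Variance = 14.75 − 3.65² = 1.4275; SD = 1.195.

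**Step 2, precision (effect independent of reading, reading unrelated to prognosis).**
- Group A rate: odds 0.40/0.60 × 2.98 = 1.987, so p = 0.665.
- Without exposure: variance of the log OR = 1/(61×0.665×0.335) + 1/(69×0.40×0.60) = 0.0736 + 0.0604 = 0.1340; SE 0.37.
- With exposure, Group A's term is multiplied by 1 + 2.65²/1.4275 = 5.92: 0.0736×5.92 + 0.0604 = 0.496; SE 0.70.
- Approximate power = Φ(ln 2.98/SE − 1.96): Φ(1.092/0.366 − 1.96) = 85% without and Φ(1.092/0.704 − 1.96) = 34% with.
- Simulation agrees: OR 3.00 vs 2.97, SE 0.37 vs 0.71, power about 87% vs 32%.

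**Step 3, effect carried by reading.** Spread the log OR over reading: 1.092/2.65 = 0.412 per level. The exposure term takes all of it, leaving an arm log OR of 1.092 − 2.65×0.412 = 0, so OR 1. Simulated: about 3.0 with 86% power without exposure; about 0.97 with 4-5% rejection with it.

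**Step 4, no effect, but readers differ in prognosis.** Take prognosis as worth 0.6 log-odds per SD and let r be its correlation with reading. The exposure slope is about 0.6r/1.195 per level, so the arm OR is about exp(−2.65 × 0.6r/1.195) = exp(−1.33r).

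| r | formula | simulated arm OR | rejection |
|---|---|---|---|
| 0.3 | 0.67 | 0.69 | 7% |
| 0.5 | 0.51 | 0.55 | 11% |
| 0.7 | 0.39 | 0.43 | 18% |
| 1.0 | 0.26 | 0.26 | 37% |

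Without exposure, a simulated null case (0.8 log-odds per SD) gave OR 0.99 and 4.7% rejection.

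**Step 5, the longitudinal model.** A simulated repeated-measures (GEE) analysis over months 0 to 18, with a lasting effect, gave a pooled arm OR of 1.22 without exposure and 0.99 with it (0.86 when reading is related to prognosis at 0.8 log-odds per SD). The pooled term is already far below 2.98 without exposure, because Group B receives the intervention after month 3.

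**The case against.** *The stated model is longitudinal and Group B is treated after day 90.* This stands. A reader might infer that exposure exists only because of arm; over 18 months it depends on arm and time together. The argument is exact only for the first 90 days, and the month-3 figures must not be read as the size of the distortion in a pooled model, where the change is from 1.22 to 0.99.

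*In a delayed-start trial, an exposure term is simply the time-varying treatment indicator.* That would be true of scheduled delivery, which is fixed by allocation and time since randomisation. It is not true of reading, which the participant chooses.

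*The sizes are assumed.* This stands. The article gives no control rate, reading distribution, link between reading and prognosis, or coding of Group B during the delay. A reader might infer that the plan would commonly show harm from a useless intervention. The lowest odds ratio, 0.26, needs reading to track prognosis perfectly; at a correlation of 0.3 it is 0.69 with 7% rejection.

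*The sentence may list predictors used across several models.* Possible, since the article speaks of analyses in the plural. One joint model is the more natural reading; if separate models were meant, the text should say so.

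*The optional post-intervention messages.* A reader might infer that their analysis repeats the fault, since "additional analyses were carried out to estimate the observed effect(s) of receiving these postintervention text messages" concerns messages that women chose to receive. It does not: these analyses are conditional extras outside the primary model, and the same section elsewhere calls them associations. Only the wording is uneven.

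**Conclusion.** The concern holds for the arm-plus-exposure model in the first 90 days. That the arm coefficient is not the randomised effect there follows from the design, given that Group B is coded as reading none. How far it departs depends on assumptions: nearly complete loss of the effect if reading carries it; no bias but a fall in power from about 87% to 32% if reading is irrelevant to effect and prognosis; and a spurious odds ratio between about 0.69 and 0.26 under the null for reading-prognosis correlations of 0.3 to 1.0. The documents therefore do not support saying that the adjustment always biases the estimate. Even in the most favourable case it costs most of the power. Because this is the specified primary analysis and no exposure-free arm comparison is stated beside it, it should be changed before analysis.

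**What to change.** Define the primary estimate as the comparison by randomised arm without the exposure term, either at month 3 or through an arm-by-time term in the repeated-measures model. Removing exposure alone is not enough, because a single pooled arm term is diluted once Group B is treated.

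Move exposure to an analysis labelled exploratory: a dose-response within Group A, or a complier-type estimate at month 3 with arm as the instrument. State how Group B's exposure is coded during the delay. If separate models were intended all along, say so.

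As an editorial matter, use the term association throughout for the opt-in messages.

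The cost is analysis wording only. No new data are needed, the exposure analysis is kept, and the Results section says primary analyses start only after follow-up ends.
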